## 2.2 Secondary Objectives

1. To determine whether a punctuated six-month course of ARV therapy during treatment of active TB will improve the response to antituberculous therapy, as measured by one and two month culture conversion, treatment failure, and relapse TB, among patients with active TB and CD4+ cell count above 350 cells/µL.
2. To determine whether a punctuated six-month course of highly active ARV therapy is safe when given with antituberculosis therapy as measured by development of ARV drug resistance, toxicity and side effects, and paradoxical reactions.

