**Table 3. Daily dosages for standard first line anti-TB drugs**

| **Drug** | **Body weight**  **< 50 kg** | **Body weight**  ** 50 kg** |
| --- | --- | --- |
| Isoniazid | 300 mg/d | 300 mg/d |
| Rifampicin | 450 mg/d | 600 mg/d |
| Ethambutola | 800 mg/d | 1200 mg/d |
| Pyrazinamide | 1.5 gm/d | 2 gm/d |

a  15 mg/kg/d

If a patient who initially weighs < 50 kg gains weight during treatment such that he or she weighs  50 kg, the patient’s doses will be increased according to the dosing chart. Pyridoxine 50 mg PO will be administered daily to all subjects during TB treatment to prevent INH-related neurotoxicity.

## 5.2 Study Intervention – Step 2

When eligibility for Step 2 is confirmed, patients will be randomized to receive either immediate six-month punctuated ARV treatment consisting of abacavir, zidovudine, and lamivudine (as Trizivir®) or continuation of anti-TB treatment only with delayed, open-label ARV treatment regimen. Randomization will occur at the time the patient is assessed and meets criteria to start the Trizivir-based punctuated ARV intervention.

Patients will be evaluated at entry into Step 2 with the following pre-ARV (baseline): assessment

1. HIV RNA Roche Amplicor;
2. Plasma storage;
3. PBMC storage/ immune function (Flow cytometry to assess cell surface activation markers, EliSpot to assess CD4 and CD8 T cell specificity to HIV and microbial peptides, Whole blood assays to determine antigen specific response to HIV and microbial antigens)

and, initiated either on the study intervention of six-month punctuated course of Trizivir® or continue with anti-TB treatment only, according to randomized assignment.

Antiretroviral therapy will be started regardless of random assignment in the intervention period when either 1) two CD4+ counts (within 3 months) drop to < 250/µL or 2) an AIDS-defining condition develops as defined by WHO stage IV AIDS-defining condition or a definitive diagnosis of a severe bacterial infection that meets WHO Stage 3 classification (Appendix II). Subjects who do not reach a study outcome during the study period will not enter Step 3 and therefore not be offered daily ARV therapy.

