#### **10.2.2.2 Specific Aim 2**

To determine whether a punctuated six-month course of ARV therapy during treatment of active TB will improve the response to antituberculous therapy, as measured by one month culture conversion, treatment failure, and relapse TB, among patients with active TB and CD4+ cell count above 350 cells/µL.

The analysis of this Specific Aim will include only patients with active TB that have been randomized in the clinical trial. The effect of ARV treatment on the response to antituberculous therapy will be evaluated by comparing the proportion of subjects with negative smears or cultures at one and two months (chi square test). A similar analysis will be performed for antituberculosis treatment failure in the ARV treatment arms compared to the reference arm.

Previous published studies of TB in HIV infection estimate relapse rates between 3 and 10%; we thus expect to identify between 10 to 35 relapse cases of TB during the study. The cumulative incidence of TB relapse will be estimated by group using Kaplan-Meier methods; incidence density methods will also be used to measure the number of relapses per 100 person-years of observation after completing antituberculous treatment according to ARV treatment group. The incidence density ratio (95% confidence interval) will be estimated to compare incidence in treated and reference groups. Cox regression analysis will be used to determine whether punctuated ARV therapy is associated with relapse after adjusting for covariates. The analysis will account for the different treatment histories by using time-dependent Cox proportional hazards analysis. The analysis will be further stratified according to relapses due to reactivation and reinfection based on the RFLP patterns.

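### The Aim 2 Cox model for TB relapse is to account for treatment histories by time-dependent Cox, so its arm coefficient is not the effect of the randomized strategies, and the plan does not say which relapse analysis decides

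*Protocol*

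**What the plan says.** The secondary objective in section 2.2 is "To determine whether a punctuated six-month course of ARV therapy during treatment of active TB will improve the response to antituberculous therapy", with relapse among the measures. Section 10.2.2.2 lists these relapse analyses:

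- Kaplan-Meier by arm: "The cumulative incidence of TB relapse will be estimated by group using Kaplan-Meier methods".
- Person-time rates by arm: "The incidence density ratio (95% confidence interval) will be estimated to compare incidence in treated and reference groups".
- Regression: "Cox regression analysis will be used to determine whether punctuated ARV therapy is associated with relapse after adjusting for covariates".
- Directly after that: "The analysis will account for the different treatment histories by using time-dependent Cox proportional hazards analysis".

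The section does not define treatment histories, does not say which variable changes with time, and does not say which analysis answers the objective. The Cox model is the only one introduced as determining whether punctuated ARV is associated with relapse. No log-rank test is named for relapse, although one is named for the primary outcome (10.2.2.1) and for time to first safety event (10.2.2.3).

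On later ARV, section 5.2 says: "Antiretroviral therapy will be started regardless of random assignment in the intervention period when either" two CD4 counts within three months fall below 250, or a qualifying clinical event occurs. Intention to treat is stated for Aim 1 (10.2.2.1) and for the primary analysis (10.2.2.4). It is not stated for the relapse model.

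**The concern.** Step 3 ARV is part of both randomized strategies. Its trigger is, apart from death, the primary endpoint (6.1), which punctuated therapy is meant to postpone. Time on Step 3 ARV is therefore a consequence of randomization. It also follows low CD4, a plausible marker of relapse risk.

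An ordinary Cox model with arm plus time-dependent ARV holds that consequence fixed. Its arm coefficient is not the effect of assigning one strategy rather than the other. It is not a clean direct effect either, because CD4 drives both the start of ARV and, plausibly, relapse. If this model were taken as the answer to Aim 2, the relapse conclusion would no longer rest on the randomization.

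**Working it through.** **1. The plan's own figure.** Section 10.2.2.2 says "Previous published studies of TB in HIV infection estimate relapse rates between 3 and 10" percent and "we thus expect to identify between 10 to 35 relapse cases of TB during the study". With 350 randomized, 350 × 0.03 = 10.5 and 350 × 0.10 = 35. The figure reproduces.

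**2. Which treatment varies over relapse risk time?** Relapse requires a completed course of TB treatment (6.2.6), which lasts six months (5.1.1.1). Punctuated ARV starts 2 to 4 weeks into TB treatment (4.4) and lasts six months (3.1). It therefore overlaps relapse risk time by only about 2 to 4 weeks. The rest of the varying treatment is essentially Step 3 ARV.

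**3. How unequal is Step 3 ARV between arms?**

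Inputs from section 10.1 and the Synopsis:
- reference-arm progression of 50% at 2 years, or at 3 years
- an effect size of 35%, read as a progression hazard ratio of 0.65
- 3-year accrual, 5% dropout per year, constant hazard
- at least 2 years of follow-up in a 5-year study, taken as uniform between 2 and 5 years

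Simplifications: ARV starts at progression, and progression by death is not separated out. The simulated share f of risk time (from month 6) spent on Step 3 ARV is:

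| Reference-arm progression | f, reference | f, punctuated |
|---|---|---|
| 50% at 2 years | 0.481 | 0.356 |
| 50% at 3 years | 0.363 | 0.258 |

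**4. Effect on the arm coefficient.** Let k be the factor by which Step 3 ARV multiplies relapse hazard. The documents give no value, so k = 0.2 to 0.7 is assumed. Let d be the arm hazard ratio (HR) adjusted for ARV. Averaging hazards over risk time:

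strategy HR = d × [1 − f_punct(1 − k)] / [1 − f_ref(1 − k)]

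Example with 50% at 2 years and k = 0.2: (1 − 0.356 × 0.8) / (1 − 0.481 × 0.8) = 0.715 / 0.615 = 1.16. If the strategies are equal, d = 1/1.16 = 0.86. If d = 1.00, the strategy HR is 1.16.

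| k | Adjusted HR when strategies are equal (2 y / 3 y) | Strategy HR when adjusted HR is 1.00 (2 y / 3 y) |
|---|---|---|
| 0.7 | 0.96 / 0.97 | 1.04 / 1.04 |
| 0.5 | 0.92 / 0.94 | 1.08 / 1.06 |
| 0.35 | 0.89 / 0.92 | 1.12 / 1.09 |
| 0.2 | 0.86 / 0.89 | 1.16 / 1.12 |
| 1.0 | 1.00 / 1.00 | 1.00 / 1.00 |

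**5. The opposite direction.** A separate CD4-driven simulation used 200,000 per arm. Relapse risk rose as CD4 fell (gradient assumed) and late ARV had no effect of its own. The by-arm HR was 0.915 and the ARV-adjusted HR 0.974. Starting ARV stands in for low CD4, so adjusting for it removes part of a real benefit.

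**6. Consequence at the planned number of events.** With E relapses and 1:1 allocation, SE(log HR) ≈ 2/√E. At two-sided 0.05, the chance of declaring benefit when the strategies are equal is Φ(−ln d × √(E/4) − 1.96).

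- d = 0.86, E = 35: 0.151 × 2.958 = 0.446, and Φ(−1.514) = 6.5%.
- d = 0.86, E = 10: 0.151 × 1.581 = 0.238, and Φ(−1.722) = about 4.2%.
- Over k = 0.2 to 0.7 and both progression scenarios: about 2.8 to 4.2% at 10 relapses and 3.2 to 6.5% at 35, against a nominal 2.5%.

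A comparison by arm that ignores later ARV stays at HR 1.00 and about 2.5%.

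**The case against.** **Randomized comparisons are already planned.** A reader might infer that Aim 2 has no valid relapse comparison. The text does not support that: Kaplan-Meier by group and an incidence density ratio with a confidence interval both compare the arms as randomized, and nothing calls the time-dependent model decisive. This stands, and it narrows the point to an unranked set in which the only model framed as answering the question is the adjusted one.

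**The term is undefined.** The section never names ARV started after randomization, and covariate definitions are commonly left to a statistical analysis plan, which is not at hand. It stands that the reading is an inference and that missing detail alone would be no finding. But the method is stated, and the timing in step 2 leaves little else for it to capture.

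**The model need not create a benefit.** A reader might infer that it will report one where none exists. That is too strong. An adjusted HR below 1 with equal strategies requires late ARV to protect against relapse and punctuated ARV to have its own offsetting protective effect. The shift can also go toward the null. At 35 relapses, an HR of 0.86 has a 95% interval of roughly 0.44 to 1.67, so a shift of this size would seldom decide the result. All of this stands.

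**Adjusting for later ARV can be a fair supplementary question.** This also stands. It justifies an exploratory label rather than deletion.

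**Conclusion.** The point holds in limited form. The relapse Cox model in 10.2.2.2, on the natural reading of treatment histories, conditions on a consequence of randomization. Its arm coefficient is then not the intention-to-treat effect, no stated safeguard covers it, and the plan does not say which relapse analysis decides.

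The shift is modest and its direction cannot be known in advance. The adjusted HR is about 0.86 to 0.97 when the strategies are equal, or hides a strategy HR of 1.04 to 1.16 when the adjusted value is 1.00. A benefit of about 0.92 becomes 0.97 when only CD4 drives relapse. False declaration of benefit rises from 2.5% to at most about 6.5%.

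These sizes rest on the protocol's progression assumptions, an assumed k of 0.2 to 0.7, an assumed CD4 gradient, and averaged hazards. If neither late ARV nor CD4 affects relapse, there is no distortion. The documents do not support the stronger readings that Aim 2 lacks any randomized relapse comparison or that a spurious benefit is likely.

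**What to change.** In section 10.2.2.2:

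1. State that the main relapse comparison is by randomized arm, using Kaplan-Meier with a log-rank test or the incidence density ratio, and a Cox model with arm and baseline covariates only. State that ARV started after randomization does not enter it, and say which of these is decisive.
2. Define treatment histories.
3. Label any analysis that adjusts for later ARV as exploratory, preferably an inverse-probability-weighted (marginal structural) Cox model that handles CD4 over time. Section 10.2.2.1 already names marginal structural models for another purpose.

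The cost is a few sentences in the protocol or analysis plan. No new data are needed, and the by-arm estimates are already planned.

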#### **10.2.2.3 Specific Aim 3**

To determine whether a punctuated six-month course of highly active ARV therapy is safe when given with anti-tuberculosis therapy as measured by development of ARV drug resistance, toxicity and side effects, and paradoxical reactions.

Safety

The safety of the study interventions, including adverse events and paradoxical reactions will be examined by summarizing the proportion, or rate, of these events according to each study arm. We will compare the cumulative proportion of grade III/IV adverse reactions and paradoxical reactions between study arms with the chi-square or Fisher’s exact test. Time until first event will also be examined using Kaplan-Meier analysis with log-rank test to compare arms. Because an individual may have more than one adverse event, we will also estimate the incidence density of adverse events in each study arm and compare these rates by determining the relative risk of adverse events (with 95% confidence intervals) in the group receiving intervention compared with the reference group.

Viral drug resistance

Descriptive analyses of drug resistance mutations in reverse transcriptase will be performed. Based on HIV RNA patterns and values, samples will be assayed from patients who exhibit viral rebound during the punctuated therapy phase and, for a subset of 20 patients 2 months after completing punctuated therapy. If resistance is identified in samples off therapy, we will assay the plasma for persistence of the mutations. We will also assess drug resistance in all specimens from patients who exhibit virologic failure (confirmed HIV RNA >200 copies/mlafter 6 months of therapy, Section 8.1.3) during the continuation phase (Step 3). Proportions and rates of drug resistance will be compared between the 2 strategies.

Analysis of Additional Outcomes

Analysis when CD4+ < 250/µL and Continuous ARV Therapy Begun

The main objective of this analysis is to determine whether punctuated ARV given during TB jeopardizes the response to continuous ARV therapy when given to participants who develop CD4+ count < 250/µL. In this analysis, there are 3 major outcomes of interest: CD4+ response, viral dynamics, and viral resistance to ARVs. Safety in terms of toxicity will also be evaluated. In terms of the CD4+ response, we will extend the linear spline model to include another knot, t**, at the time when an individual reaches CD4+ count < 250/µL. This modification of the model will allow us to compare the slope among patients who received punctuated therapy and those who did not. Viral dynamics, viral resistance and safety will be analyzed.

Ancillary Analyses

*Immunologic and Viral Dynamics (see appendix X.)*

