| Primary  Endpoints | HIV disease progression, defined as time to:  1) CD4+ cell count decline to 250/μL or below;  2) development of an AIDS-defining condition (WHO Staging criteria); or,  3) death. |
| Secondary  Endpoints | Response to antituberculosis therapy:  sputum AFB clearance by one and two months  rates of TB treatment failure  rates of TB relapse  microbiologic cure of TB  Safety:  Development of antiretroviral drug resistance  Toxicity and side effects  Paradoxical reactions |
| Statistical &  Analytic Plan | The sample size for the trial is 350 HIV-infected TB patients - 175 randomized to punctuated therapy and 175 randomized to anti-TB treatment only and delayed ARV therapy. The sample size provides a power of 80 – 90% to detect an effect size of 35% or greater for HIV disease progression. This effect size translates into an average delay of about one year before the need to start ARV therapy.  The intent-to-treat approach will be used to compare the rate of HIV disease progression between TB patients randomized to receive either punctuated or delayed ARV therapy.  Analysis – Specific Aim 1  The primary outcome for the study is HIV disease progression. The primary analysis of the study will compare  The failure-time distribution of the treated to the reference group.  The change in CD4+ count over time in each group.  Life-table, failure-time, and repeated measures methods will be used to analyze the data.  Analysis – Specific Aim 2  The effect of ARV treatment on the response to antituberculosis therapy will be evaluated by comparing  The proportion of subjects with negative smears or cultures at one and two months (chi square test).  Treatment failure rates between groups  Relapse tuberculosis rates  Life-table, failure-time, and person-year methods will be used in this analysis.  Analysis – Specific Aim 3  The safety of the study intervention will be examined by summarizing the incidence rate and cumulative proportion of severity grade III/IV adverse events according to each study arm.  Life table and descriptive methods will be used.  Additional analyses  In addition to these analyses, the study will examine viral dynamics, emergence of antiretroviral drug resistance, and reconstitution of the host immune response. |

#

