## 10.2 Analytic Strategy

### **10.2.1 Descriptive Analysis**

A descriptive analysis will examine the distribution of continuous variables and the frequency histograms for categorical variables. In non-normal distributions, such as viral load, transformations will be used to normalize the data for statistical analysis. To assess the adequacy of randomization, baseline characteristics of the study groups will be compared using Wilcoxon rank sum test (students t-test for normal distributions) for continuous data or chi-square test for categorical data.76 Where the expected frequencies are small, exact methods may be used. Cumulative incidence of events (e.g., CD4 < 250, relapse TB) will be estimated as the number of events per population at risk at baseline for each treatment group; 95% confidence intervals will be determined using standard methods.77 Incidence density will be estimated as the number of new, or incident, events per 100 person-years of observation; appropriate 95% confidence intervals can be calculated.77 The clinical course of HIV infection will be characterized as the incidence density of opportunistic infections following the diagnosis of active TB. The relative risk of opportunistic infections in the treatment versus the reference groups will be estimated with 95% confidence intervals.77 Statistical analysis will be performed using SAS and S-Plus statistical packages.

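### The adverse-event rate ratio counts repeat events in a patient but names no allowance for within-patient correlation, so its usual 95% interval would be too narrow if patients differ in risk

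*Protocol*

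**What the plan says.** Section 10.2.2.3 plans three safety comparisons. Two use one outcome per patient: "We will compare the cumulative proportion of grade III/IV adverse reactions and paradoxical reactions between study arms with the chi-square" or Fisher's exact test, and "Time until first event will also be examined using Kaplan-Meier analysis with log-rank test to compare arms". The third is added because events repeat: "Because an individual may have more than one adverse event, we will also estimate the incidence density of adverse events in each study arm". The arms are then to be set against each other: "compare these rates by determining the relative risk of adverse events (with 95% confidence intervals" are the only inferential detail given.

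Section 10.2.1 defines the measure: "Incidence density will be estimated as the number of new, or incident, events per 100 person-years of observation". On precision it adds only that "appropriate 95% confidence intervals can be calculated", with a textbook citation. The same section plans a rate for opportunistic infections and says "The relative risk of opportunistic infections in the treatment versus the reference groups will be estimated with 95% confidence intervals".

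The synopsis describes the Aim 3 summary as "summarizing the incidence rate and cumulative proportion of severity grade III/IV adverse events according to each study arm". The incidence-density sentence in Section 10.2.2.3 carries no grade limit. Nowhere does the protocol give an expected adverse-event rate, a mean number of events per patient, or a measure of how unevenly events fall across patients.

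**The concern.** Incidence density is offered as the answer to repeat events. It does use all the events, but dividing a total count by total person-time does nothing about their correlation. The ordinary interval for a ratio of two such rates depends only on the two event totals, and is correct only if events occur independently at one rate per arm. If some patients are more prone to events than others, the totals vary more between trials than that interval allows. The feature that motivates the method is therefore the one that undermines its usual standard error.

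The protocol itself anticipates recurrence in the same patient. Sections 8.1.2.1.2, 8.1.2.2.2 and 8.1.4.2.3 all deal with restarting a drug and with an event returning. Adverse-event surveys run through Step 2 and Step 3 for up to five years (Sections 7.3.2, 7.3.3 and 7.4.2), so repeat counts can accumulate.

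At stake is the only planned safety comparison that uses every event. A few patients with many events could make the arms appear to differ, in either direction, on Aim 3.

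**Working it through.** There is no figure in the protocol to reproduce for this comparison, so the check asks how far the usual interval can be off and under what conditions.

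**Inputs from the protocol.** 175 patients per arm (Section 10.1); follow-up of at least 2 years (synopsis) and at most 5 (Section 7.3.3); 5% dropout per year (legend to Figure 5); a 95% interval.

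**Assumed inputs.** Event rate per year and between-patient variance of the rate (gamma frailty with mean 1). The protocol gives neither.

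**Step 1: the usual interval.** With a and b events, the log rate ratio has SE = sqrt(1/a + 1/b). If the variance of a patient's event count is φ times its mean, the true SE is larger by sqrt(φ). The chance that the interval excludes 1 when the arms do not differ is

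2 × [1 − Φ(1.96/√φ)].

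| φ | 1.96/√φ | True error | Interval should be wider by |
|---|---|---|---|
| 1 | 1.960 | 0.050 | 1.00 |
| 1.2 | 1.789 | 0.074 | 1.10 |
| 1.5 | 1.600 | 0.110 | 1.22 |
| 2 | 1.386 | 0.166 | 1.41 |
| 3 | 1.132 | 0.258 | 1.73 |

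(The last column is √φ, on the log scale.) For gamma frailty and equal follow-up, φ = 1 + (mean events per patient) × (frailty variance). A mean of 0.5 events with variance 1 gives φ = 1.5; a mean of 1 with variance 1 gives φ = 2.

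**Step 2: an example.** Take a mean of 0.5 events per patient, so 175 × 0.5 = 87.5 events per arm, with equal person-time. The usual SE is sqrt(2/87.5) = 0.151. At an observed ratio of 1 the interval is exp(±1.96 × 0.151), or 0.74 to 1.34. With φ = 1.5 the SE is 0.151 × 1.22 = 0.185 and the interval is 0.70 to 1.44.

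**Step 3: simulation with unequal follow-up.** No true difference, 175 per arm, follow-up uniform on 2 to 5 years with 5% yearly dropout, 10,000 trials per setting. The robust variance of the log ratio is the sum over arms of Σ(y − r·t)² / (Σy)², where y is a patient's count, t the person-time and r the arm's rate.

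| Events per year (assumed) | Usual interval, frailty variance 0 | 0.5 | 1 | 2 |
|---|---|---|---|---|
| 0.05 | 0.046 | 0.059 | 0.067 | 0.087 |
| 0.1 | 0.050 | 0.062 | 0.091 | 0.128 |
| 0.3 | 0.048 | 0.115 | 0.169 | 0.264 |
| 0.5 | 0.050 | 0.153 | 0.242 | 0.359 |
| 1 | 0.051 | 0.243 | 0.368 | 0.491 |
| 2 | 0.051 | 0.353 | 0.499 | 0.614 |

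With the robust variance the error is 0.046 to 0.062 across all 24 settings. With no between-patient variation the usual interval is correct. Otherwise the excess grows with both the event rate and the variation between patients.

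**The case against.** The strongest reply is that the protocol never says the interval treats events as independent. It asks for appropriate intervals and names no variance estimator, and a patient-clustered interval would comply with that wording. Such detail is often left to an analysis plan, and none is shown here. This stands as far as it goes: independence is the default reading of a textbook person-time interval, not a quoted commitment. What remains is that the protocol raises repeat events, presents incidence density as the way to handle them, and stops there. For repeated CD4+ counts Section 10.2.2.1 does specify a mixed-effects model.

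Second, the rate ratio is supplementary. The proportion and first-event comparisons count each patient once and are sound on this point, no test or decision rule is attached to the rate ratio, and the stopping boundary in Section 10.3 concerns HIV disease progression. All of this stands and limits the consequence.

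Third, a reader might infer that opportunistic infections are also counted repeatedly. Section 10.2.1 does not say so. It speaks of new, or incident, events, and the repeat-event rationale is given only for adverse events. A first-event count is at least as natural a reading.

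Fourth, a reader might want one multiplier, such as false differences being two to seven times too frequent. That range requires φ between about 1.42 and 4.40, and the protocol gives no basis for it. If only grade III/IV events are counted and they are rare, say 0.05 to 0.1 per year, the simulated excess is 1.2 to 2.6 times for the non-zero frailty variances tried; at higher rates it can exceed seven times.

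**Conclusion.** The point holds for the adverse-event incidence-density ratio in Section 10.2.2.3, as a minor correction. Calculated in the usual way, its 95% interval is too narrow whenever patients differ in event risk. The true two-sided error of the nominal 5% comparison is 5% with no such variation, and about 7%, 11%, 17% and 26% at variance-to-mean ratios of 1.2, 1.5, 2 and 3. These ratios are assumptions, and which of them applies cannot be read from the protocol. The conclusion also rests on the plain person-time interval being the one used.

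The documents do not support extending this to opportunistic infections without knowing whether repeats are counted. Nor do they support any doubt, on this ground, about the chi-square or Fisher comparison, the first-event analysis or the primary analysis.

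**What to change.** In Section 10.2.2.3, keep the adverse-event incidence-density ratio and state that its 95% interval uses a variance clustered on the patient. Either a log-linear rate model with log person-time as offset and a robust variance, or a negative binomial model with the same offset, would serve. State also whether the ratio covers all grades or only grade III/IV, since the synopsis and this section differ.

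In Section 10.2.1, say whether a second opportunistic infection in the same patient is counted. If it is, use the same variance for that ratio; if only first infections count, nothing need change there.

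The cost is a sentence or two in the plan and one model option in the software, with no new data. Intervals will be wider where events cluster, by √φ on the log scale: about 1.2 times at a variance-to-mean ratio of 1.5 and 1.4 times at 2.
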